## Abstract

**Introduction:**

Risk thresholds for using statins to prevent cardiovascular disease (CVD) have recently been lowered, so an increasing number of patients are now prescribed these drugs. Although the safety of long-term statin use has been generally established, concerns about the balance of risks and benefits of statins still exist for some medical professionals and patients, and issues concerning their side effects are occasionally widely publicised. This study will report the rates of stopping for statins and also identify any patient groups more likely to stop using statins, so possibly increasing their risk of cardiovascular events.

**Methods and analysis:**

A prospective open cohort study between 1 January 2002 and 30 September 2014 will be based on the general population of people prescribed statins, using records from UK general practices contributing to the Clinical Practice Research Database (CPRD). Participants aged 25–84 years will enter the cohort on the date of their first prescription for a statin and leave on the earliest date of: a cardiovascular event; death; leaving the practice; the last practice upload date or the study end date. If there are no prescriptions within 90 days after the expected finishing date of a prescription, a patient will be defined as a stopper with the discontinuation outcome date as the expected finishing date. Rates of statin discontinuation will be calculated by calendar year, type and dose of statin, age, and morbidities. Cox proportional regression analyses will be run to identify the most important factors associated with discontinuation. Analyses will be run separately for patients without CVD (primary prevention) and with diagnosed CVD (secondary prevention).

**Ethics and dissemination:**

The protocol has been reviewed and approved by Independent Scientific Advisory Committee for MHRA Database Research. The results will be published in a peer-reviewed journal.

Strengths and limitations of this study
Large size and substantial statistical power.Representative study population.Uncertainty regarding adherence to statin treatment and exact date of the statin discontinuation.Possible underestimation of statin use due to over-the-counter use.Lack of information on some factors that might affect patients’ decisions to stop statins.

## Introduction

Cardiovascular disease (CVD), which includes heart attacks and strokes, has a major impact on the lives of affected individuals and treatment costs are a significant burden for health services.^1^ A high level of low-density lipoprotein (LDL) cholesterol is a significant risk factor for CVD^2^ and statins are frequently prescribed as a preventive measure to reduce cholesterol levels. In the UK in 2006, the National Institute for Health and Care Excellence (NICE) recommended statins for primary prevention in patients with a 10-year risk of CVD of 20% or more.^3^ Subsequently, the Cholesterol Treatment Trialists meta-analysis (2012),^4^ which was based on 27 trials of outcomes for statin users versus controls, demonstrated in lower risk patients a risk reduction for major vascular events of 21% per 1.0 mmol/L from LDL cholesterol level reduction, and in 2014, NICE decreased risk threshold for recommending statin prescribing to a 10-year risk of 10%.^5^ In the USA, the thresholds for using statins have also recently been lowered,^6^ so many more patients are eligible to receive prescriptions for these drugs.

The benefits of such preventive therapy are, however, dependent on the level of adherence of patients with their prescribed regime and discontinuation is an extreme form (zero adherence) of non-adherence.^7^ In general, non-adherence to prescribed medication is associated with adverse outcomes and higher costs of care.^8^ Discontinuation of statins can cause changes in platelet activity or inflammation, impair vascular homoeostasis or lead to endothelial dysfunction and may, therefore, independent of changes of cholesterol levels, increase risk of cardiovascular events.^9^ A number of studies in patients with acute cardiovascular conditions have demonstrated problems associated with statin withdrawal. In one, hospitalised patients who discontinued statins were found to have a three times higher rate of myocardial infarction (HR 2.93, 95% CI 1.64 to 6.27) than patients who continued to receive statins.^10^ Other studies have demonstrated that stopping statins after an acute cardiovascular event increased mortality risk or worsened the outcome.^11^
^12^ One randomised controlled trial in patients with stable cardiac conditions found no significant differences in rates of cardiac events or deaths from heart disease associated with statin discontinuation, but the number of actual events was too low to allow for the effect of statin non-adherence—24 in the prior 6-week wash-out period compared with 31 in the 8-week therapy period.^13^

However, while statin therapy is associated with decreased mortality and fewer complications related to atherosclerosis for patients already diagnosed with CVD, this has not been established for patients without CVD. Statins also have side effects and a number of studies have demonstrated these,^14^ which include increased risks for diabetes^15^
^16^ and myopathy.^17^
^18^ With respect to their effectiveness in patients without CVD, a meta-analysis of 11 randomised controlled trials reported no significant associations between statin use and mortality risk for such patients (risk ratio 0.91, 95% CI 0.83 to 1.01).^19^ A later meta-analysis, investigating the effect of cholesterol-lowering therapy on all-cause mortality, did show a significantly reduced risk for patients without CVD (risk ratio 0.91, 95% CI 0.88 to 0.93).^4^ However, as highlighted in a subsequent secondary analysis, this reduced mortality was not demonstrated for the subgroup with low cardiovascular risk (0.95, 0.86 to 1.04 for CVD risk <10%).^20^ Moreover, the original finding might simply have reflected a healthy-user bias because a study investigating the risk of accidents associated with adherence to statins^21^ has shown adherent patients to be less likely to be involved in accidents (HR 0.85, 95% CI 0.83 to 0.87) and more likely to use screening services (1.17, 1.15 to 1.20).

While the safety of long-term statin use has, therefore, been supported by systematic reviews,^4^
^22^ issues about their side effects, effectiveness and the balance of risks and benefits, especially for people at low risk of CVD, have occasionally been widely publicised.^20^
^23^ So concerns do still exist among some medical professionals and their patients, and statin non-adherence and discontinuation seem likely to rise as more low-risk patients are included, who have no symptoms and might regard such preventive medications as unimportant or risky.^24^
^25^

Non-adherence to drug treatments is, however, a many-layered issue, which can be related to a poor healthcare system, the type of condition, patient characteristics, the complexity or side effects of the therapy, or specific socioeconomic issues for a treatment group.^8^ For statins in a UK study environment, issues to do with the health system or cost of treatment are unlikely to be significant. Taking statins by themselves is also not a complex therapy, although issues arising from polypharmacy or other patient characteristics might well cause discontinuation. Rates of non-adherence to statins in cardiovascular patients has, however, been shown to be 26%,^26^ while a recent American study has reported that more than 50% of statin users stopped treatment at least temporarily.^27^

The proportion of patients who discontinue statins and their reasons for doing so are not, however, clear. Discrepancies between randomised controlled trials and observational studies have been shown in a meta-analysis,^28^ which reported for randomised trials a 90.3% (95% CI 89.8% to 90.8%) adherence at 1-year follow-up against 49% (95% CI 48.9% to 49.2%) for observational studies. This high adherence found in randomised controlled trials is clearly related to the enrolling of selected populations and provision of a form of monitoring for the included patients. Observational studies provide a much closer reflection of the real world, but the very high levels of discontinuations suggest that many may not be due to statin-related events, and this has led to a number of studies investigating patterns of discontinuation and the causes.

Of these, all seem to have concentrated on patients with already diagnosed CVD, and most were conducted either before the most recent CVD guidelines were issued or UK-derived CVD risk estimation was available. One study, based on Clinical Practice Research Database (CPRD) data, which showed an association between discontinuation and higher total mortality following acute myocardial infarction,^29^ has also provided information about prevalence of comorbidities with respect to different patterns of statin use. Another CPRD study has investigated the factors associated with discontinuation,^30^ but this study was conducted in 2002. This assessed discontinuation risks in a mixed group of patients, but having only 20% of the cohort without diagnosed CVD and following up patients for only 1 year. It has also been noted that further research is needed particularly for patients with low cardiovascular risk.^31^

While there have been observational studies examining the pattern of uptake of statins^32–34^ and of unintended effects from statin use,^35–37^ relatively few studies have examined the discontinuation of statins. We have, therefore, designed a study that will follow statin users in the UK over time, report the rates of stopping for statins with the discontinuation outcome based on prescription data, and look at whether these have changed with time or differ across statin types. The study will also identify any patient groups more likely to stop statins and so possibly increase their risk of CVD.

## Methods and analysis

### Data source

We will use data from 664 UK general practices contributing to the CPRD (http://www.cprd.com). The practices are spread across the UK, and their registered patients have been shown to be representative of the general population.^38^ Data are routinely collected and the recorded information includes demographics, patient characteristics, clinical diagnoses, symptoms and prescribed medications. The database has been validated using other sources of information in the UK and has been used for similar studies for statin discontinuation.^29^
^30^

### Sample selection

This will be a prospective open cohort study of new statin users identified during the study period between 1 January 2002 and 30 September 2013. Incident cases who discontinued statin therapy will be identified during follow-up. Patients will enter the cohort on the date of their first recorded statin prescription within the study inclusion period. Patients will be followed up until the earliest of: death; deregistration with the practice; last upload of computerised data; 1 year from the date the study inclusion period ended. Patients will be subdivided into two groups evaluated on the date when they started taking statins: those without CVD records before the entry date (taking statins for primary prevention); those with CVD diagnosed at or before entering the study (taking statins for secondary prevention). Patients without CVD at the baseline date will be followed up until the time of a CVD diagnosis if it occurs before the study exit date.

We expect the rate of discontinuation to be lower in the secondary prevention group, and this subdivision will make our results more easily comparable with existing studies.

### Inclusion criteria

Eligible patients will be aged 25–84 years at the study entry, have at least two prescriptions for a statin in the study period and have at least 1 year of records prior to entry—calculated from the later date of: the date of registering with a general practice or the earliest date of upload of computerised practice data—and at least 1 year of follow-up—calculated from their first statin prescription in the study period. Patients with one or more prescriptions for statins in the 12 months prior to cohort entry will be excluded. Cerivastatin will not be included in the study because it was withdrawn from the market in August 2001, but patients with prescriptions for it in the 12 months prior to cohort entry will be excluded.

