### Exposure

A number of statin users will have only one prescription before stopping. Because they did not receive a repeat prescription, it cannot be certain that these patients actually ever took statins. So, for the main analysis, having excluded patients with one prescription, we will run a sensitivity analysis including all patients with one or more prescriptions. We will report on the percentage of patients that had only one prescription and describe characteristics of this group.

The following statins will be included into the analysis: atorvastatin, simvastatin, fluvastatin, pravastatin and rosuvastatin. As the statin most commonly prescribed in the overall study period, simvastatin—used by around 70% of patients—will be used as the reference drug.

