### Outcome

The outcome will be defined as a discontinuation of statin use if there are no prescriptions within the 90 days following the expected finishing date of a prescription. The first such event will be considered as an outcome, and further prescriptions will not be used in the analysis of discontinuation. A 90-day exposure window has been used in other CPRD studies^29^
^30^ because it is the longest prescription length that can be issued in the UK. The date of the outcome will be defined as the expected finishing date of the prescription.

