### Additional analyses

Patients might discontinue statins within the first year or after a longer period. The characteristics of these patients might differ, so we shall rerun the main analysis twice, in the first censoring all patients who did not discontinue before the end of year one, and in the second removing all patients who did discontinue before the end of year 1.

Some statin users have discontinuous use, with one or more restarts against a background of fairly continual usage. We shall define a subcohort in the study period for patients who discontinued statins (the outcome date in the main analysis will be their new entry date) and follow them until they have a new statin prescription or they are censored as described in the Study design section. We shall describe how many people restarted statin therapy within the first 6 months, 7–12 months and 12 or more months after their new entry dates using Kaplan-Meier estimates. We shall report descriptive statistics for the covariates listed above both for stoppers who restarted and those who did not.

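### The two-prescription rule sets no time limit on the second prescription, so whether a first-prescription stopper is in the main analysis depends on a prescription issued after the outcome

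*Protocol article*

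**What the plan says.** Four parts of the protocol article bear on this.

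- **Sample selection** sets time zero: "Patients will enter the cohort on the date of their first recorded statin prescription within the study inclusion period".
- **Inclusion criteria** require that patients "have at least two prescriptions for a statin in the study period". Nothing says how soon the second must follow the first.
- **Outcome** defines discontinuation as "no prescriptions within the 90 days following the expected finishing date of a prescription". This applies to any prescription, including the first. On dating: "The date of the outcome will be defined as the expected finishing date of the prescription". On what follows: "The first such event will be considered as an outcome, and further prescriptions will not be used in the analysis of discontinuation".
- **Exposure** gives the reason for leaving out one-prescription patients: "Because they did not receive a repeat prescription, it cannot be certain that these patients actually ever took statins". It adds that "we will run a sensitivity analysis including all patients with one or more prescriptions", and that the size and characteristics of the one-prescription group will be reported.

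The restart analysis under **Additional analyses** starts from the main-analysis outcomes: "We shall define a subcohort in the study period for patients who discontinued statins", with the outcome date as the new entry date.

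**The concern.** Eligibility should be settled by what is known at or before the start of follow-up, or at least before the outcome. Here, for anyone with a 90-day gap after the first prescription, it is settled by what happens after the outcome date. Among first-prescription stoppers, the main analysis keeps those who later return and drops those who do not.

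Three planned outputs are exposed.

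- **Hazard ratios.** A covariate linked to returning can look like a predictor of stopping. Identifying groups more likely to stop is a stated aim. The rerun that looks only at stopping in year one is the most exposed, because first-prescription stoppers form part of its events.
- **Calendar year.** Early entrants have up to about 12 years in which to qualify by returning; the last entrants have about a year or less. Change over time is also a stated question.
- **Restart proportions.** The first-prescription stoppers who reach the restart subcohort are nearly all restarters, because returning is what let them in.

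**Working it through.** **Step 1. Two patients with the same history up to the outcome**

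| | Patient A | Patient B |
|---|---|---|
| First prescription (time zero) | yes | yes |
| 90 days without a prescription after its expected finish | yes | yes |
| Outcome under the Outcome section | stopped, end of prescription 1 | stopped, end of prescription 1 |
| Later prescription in the study period | none | one, possibly years later |
| Count under the Inclusion criteria | 1 | 2 |
| In the main analysis | no | yes, as a stopper |

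Doubt that prescription 1 was taken is the same for A and B. Only the post-outcome prescription separates them.

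**Step 2. Inputs**

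The plan gives no figure on this point to reproduce, and its sample-size figures do not enter. Let p be the share of new users who stop after the first prescription and r the share of those who later return. Neither is in the documents. Both are assumed, with p from 5% to 20% and r from 30% to 70% unless stated.

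**Step 3. First-prescription stopping as the main cohort would show it**

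The rule drops p(1−r) of new users. The observed share is p·r / [1 − p(1−r)].

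- p = 5%: 1.6% (r = 30%) to 3.6% (r = 70%)
- p = 10%: 3.2% to 7.2%
- p = 20%: 7.0% to 14.9%

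It is below p in every case.

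**Step 4. Spurious association**

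Take two groups with the same true p = 10%, returning at 60% and 40%.

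- Group 1: 0.10 × 0.60 / (1 − 0.10 × 0.40) = 0.060/0.960 = 6.25%
- Group 2: 0.10 × 0.40 / (1 − 0.10 × 0.60) = 0.040/0.940 = 4.26%
- Ratio: 6.25/4.26 = 1.47

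The ratio is 1.48 at p = 5% and 1.43 at p = 20%. With 70% v 30% returning and p = 10% it is 2.24. With equal return shares it is 1. These are ratios for stopping at the first prescription; a hazard ratio over all follow-up would be diluted by later stoppers.

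**Step 5. Restart proportion**

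Assume half of those who continue past the first prescription stop later, and that 45% of all stoppers restart. Let L = 0.5(1−p). The truth is 45%. The reported proportion is (0.45p + 0.45L) / (0.45p + L).

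- p = 2%: (0.0090 + 0.2205) / (0.0090 + 0.4900) = 46.0%
- p = 5%: (0.0225 + 0.21375) / (0.0225 + 0.4750) = 47.5%
- p = 10%: (0.0450 + 0.2025) / (0.0450 + 0.4500) = 50.0%

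**Step 6. Entry year**

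Assume 60% of first-prescription stoppers would ever return, after 118 days (a 28-day prescription plus 90 days) plus an exponential time with the mean shown, and that patients leave at 0.07 per year. With λ = 1/mean, d = 118/365.25 years and T the time from entry to the cut-off, the share kept is

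0.6 · exp(−0.07d) · [λ/(λ+0.07)] · [1 − exp(−(λ+0.07)(T−d))],

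set to zero when T < d and averaged over entry dates in the year. Sample selection ends the study period on 30 September 2013; the Abstract ends it on 30 September 2014. Both cut-offs are shown.

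| Mean further gap | Cut-off | 2002 entrants | 2011 | 2013 |
|---|---|---|---|---|
| 3 years | Sept 2013 | 48% | 26% | 2% |
| 3 years | Sept 2014 | 48% | 34% | 17% |
| 6 months | Sept 2014 | 57% | 56% | 50% |
| 3 months | Sept 2014 | 58% | 58% | 57% |

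A falling share kept would appear as a false decline in early stopping by entry year. It is large if returns are slow and close to nil if they are quick and the later cut-off applies.

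**The case against.** The strongest reply is that the plan handles this openly. It says that one-prescription patients are left out, gives a reason, will describe them, and will repeat the analysis with everyone. That repeat analysis is free of the selection, and because the Cox model contains entry year, its calendar effect is free of it too. This stands. A reader might infer that the sensitivity analysis does nothing for the hazard ratios or the trend, and that would be wrong. What remains is that the headline results are still the selected ones, and that the plan does not extend the analysis to restarts.

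A reader might also infer that the Inclusion criteria contradict the Outcome section's statement that later prescriptions are not used. They do not. That statement concerns the analysis of discontinuation after the first event and is silent on eligibility. The two are in tension, no more.

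The Exposure section can be read as describing everyone who stops after a first prescription, returners included, which would remove the asymmetry. But the operative criterion counts prescriptions over the whole study period.

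It is tempting to say that every first-prescription stopper in the restart subcohort restarts by construction. Nearly all do. A primary-prevention patient whose second prescription follows a CVD diagnosis qualifies by count but is censored at the diagnosis.

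Finally, the illustrations rest on assumed inputs, and the restart analysis is descriptive, using Kaplan-Meier estimates by interval and not the crude proportion in Step 5. Both points are fair and limit what can be said about size.

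**Conclusion.** The concern holds as a design flaw of moderate weight. Read together, the Sample selection, Inclusion criteria and Outcome sections make main-cohort membership of a first-prescription stopper depend on a post-outcome prescription, and the reason in the Exposure section does not justify the split. That conclusion follows from the wording alone.

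The direction is clear for two outputs: first-prescription stopping is understated and the restart proportion overstated. For hazard ratios the direction depends on which covariates go with returning. The size is unknown, since the documents give no stopping, return or gap figures. Under the assumptions shown, the early-stop ratio could be about 1.47 when the truth is 1, and restarting could be reported as 46% to 50% when 45% is true. The calendar-year distortion runs from near zero to large. The 2% retention for 2013 entrants should not be quoted alone: it needs both a three-year mean gap and the September 2013 cut-off.

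**What to change.** Treat all first-prescription stoppers alike, whether or not they return. Two ways are open.

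- **(a) Timely second prescription.** Require it within 90 days of the first one's expected finishing date, and start at-risk time at that second prescription. Put everyone else, later returners included, in the one-prescription group that is described and added in the sensitivity analysis.
- **(b) Everyone.** Make the one-or-more-prescriptions cohort the main analysis and the restricted cohort the sensitivity analysis.

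In either case, run the restart analysis with first-prescription stoppers all in or all out, and say which.

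No new data are needed: the prescription dates already serve the outcome, and the cohort flag has to be re-derived. Option (a) takes more than one sentence. It moves time zero, so the entry date and baseline, the 1-year follow-up rule and the year-one split must be aligned. It also estimates discontinuation only among patients with a timely repeat prescription. It keeps no first-prescription stoppers in the main analysis, so it buys consistency and does not reduce the undercount. Option (b) counts them all and keeps the present time zero, at the price of including some patients who may never have taken the drug.

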### Sensitivity analyses

Apart from the two sensitivity analyses already mentioned relating to exposure and missing values, two others will be included. One will be to facilitate comparison with the results of the Zhang *et al*^27^ study for long-term statin discontinuation. In this, we will define an outcome as an absence of any statin prescriptions within the 12 months (365 days) following the expected finishing date of a prescription. As before, the expected last date will also be the date of the outcome. Because of the longer period required for an outcome, for this analysis, we will remove patients with less than 2 years of follow-up records. The other will be run to investigate the influence of possible changes in baseline variables over the full study period, by rerunning the analysis with the follow-up period restricted to 5 years.

A 1% level of statistical significance will be used to allow for multiple comparisons. Stata V.13 will be used for all the analyses.

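### Eligibility depends on 1 year of observed follow-up after the first prescription (2 years in the 365-day-gap analysis), so patients who die or deregister early are removed rather than censored

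*Protocol article*

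**What the plan says.** Inclusion criteria (Protocol article) requires 1 year of prior records "and at least 1 year of follow-up", the latter "calculated from their first statin prescription in the study period". That prescription is also the cohort entry date.

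Sample selection recruits new users "identified during the study period between 1 January 2002 and 30 September 2013" and ends follow-up at the earliest of "death; deregistration with the practice; last upload of computerised data; 1 year from the date the study inclusion period ended". Primary-prevention patients also "will be followed up until the time of a CVD diagnosis if it occurs before the study exit date".

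Sensitivity analyses repeats the rule with a longer window for the outcome based on a 365-day gap: "for this analysis, we will remove patients with less than 2 years of follow-up records".

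Additional analyses plans a separate run for discontinuation in the first year. The four listed sensitivity analyses are: one-prescription users included, complete cases only, the 365-day gap, and follow-up capped at 5 years. None drops the follow-up requirement.

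**The concern.** Entry is at the first prescription, but whether a patient counts as having entered is known only a year later. Death and deregistration are ends of follow-up in Sample selection, yet in the first year they act as exclusions. By construction nobody in the analysed cohort dies or deregisters in year 1.

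Two things are at stake. The first is the target population. The abstract and the strengths list present the study as representative of people prescribed statins, whereas year-1 rates and curves would apply to one-year survivors still registered at the same practice. The second is the hazard ratios. If patients close to death or about to leave also stop statins more often, the rule removes them selectively from groups where early loss is common. Age 75–84, cancer, dementia and heart failure are the listed covariates most exposed. Their association with stopping could be attenuated, and nothing in the plan would show it.

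**Working it through.** **What the rule removes.** The inclusion period closes on 30 September 2013 and follow-up can run one year longer, so the last entrant has 30 September 2013 to 30 September 2014 = 365 days by the study calendar. The study end date therefore excludes nobody from the main analysis. The rule acts through the other ends of follow-up:
- death or deregistration within a year, which may be informative;
- a practice's last upload falling within a year of entry, which is largely administrative;
- possibly a first-year CVD diagnosis in primary prevention, because the text does not say whether that counts towards the 1-year requirement.

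Under the 2-year rule, entry after 30 September 2012 is a further administrative cause of exclusion.

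**Is a year needed to see the outcome?** No. The main definition needs 90 days after a prescription's expected finishing date.

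**How many are removed?** The plan gives no separate figure. The sample size section pools short follow-up with prior statin users (together just over one-third of about one million). Assume a combined rate h of death and leaving of 0.04 to 0.15 per year:
- 1 year: 1 − exp(−h) = 3.9% to 13.9%, roughly 24 000 to 84 000 per 600 000 starters;
- 2 years: 1 − exp(−2h) = 7.7% to 25.9%.

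**Illustration A: a frail minority (all inputs assumed).** A marker is present in 10% of patients. Frailty affects 25% of marker patients and 4% of others. Loss is 0.8/yr if frail and 0.05/yr otherwise. Base stopping is 0.25/yr, and the outcome needs 90 observed days. Retention after 1 year in marker patients is 0.25·exp(−0.8) + 0.75·exp(−0.05) = 0.112 + 0.713 = 0.83. Their frail share falls from 25% to 0.112/0.826 = 14%. Simulated first-year rate ratio, marker v no marker:

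| Stopping, frail v other | Without any loss | No rule | 1-year rule | 2-year rule |
|---|---|---|---|---|
| 4 times | 1.45 | 1.28 | 1.24 | 1.13 |
| 2 times | 1.19 | 1.10 | 1.10 | 1.05 |
| Equal | 1.00 | 0.97 | 1.00 | 1.00 |

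In the first row the log ratio goes from ln 1.28 = 0.247 to ln 1.24 = 0.215 under the 1-year rule (13% lost) and to ln 1.13 = 0.122 under the 2-year rule (51% lost).

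**Illustration B: stopping rises in the last 6 months of life (all inputs assumed).** There are 60 000 patients with mortality 1.5%/yr and 15 000 with higher mortality. Deregistration is 4%/yr. Stopping is 0.35/yr in year 1 and 0.08/yr after. Time at risk is cut 90 days before exit in every version. At 20%/yr mortality the 1-year rule excludes 1 − exp(−0.24) = 21% against 1 − exp(−0.055) = 5%.

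| Mortality, higher group | Rise in stopping | Ratio, no rule | Ratio, 1-year rule |
|---|---|---|---|
| 30%/yr | 4 times | 1.17 | 1.08 |
| 20%/yr | 4 times | 1.12 | 1.06 |
| 10%/yr | 4 times | 1.06 | 1.03 |
| 8%/yr | 4 times | 1.03 | 1.02 |
| 5%/yr | 4 times | 1.01 | 1.00 |
| 20%/yr | 2 times | 1.03 | 1.01 |

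The first two rows are Cox HRs. The 10% row comes from a repeat with entry dates spread uniformly. The last three rows use a stratified rate ratio in place of Cox. At 20%/yr with a fourfold rise, ln 1.12 = 0.113 falls to ln 1.06 = 0.058, so about half is lost. The overall year-1 stopping rate in that scenario moves only from 0.361 to 0.354 per year, about 2%.

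**The case against.** Several points on the other side stand.

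- A reader might infer that early stoppers are lost, or that year 1 is immortal time in the damaging sense. It is not so. Stopping does not end follow-up, so first-year stoppers who stay alive and registered are kept and counted. The rule selects on survival and registration, not directly on the outcome.
- A reader might infer that, because entry closes a year before study end, every exclusion is informative. Last upload varies by practice, so part of the exclusion is administrative.
- A reader might infer that first-year CVD events also remove primary-prevention patients. The documents leave that open.
- A reader might infer that HRs for frail groups are known to be biased downwards. That needs a link between early loss and stopping, which the document does not establish. The larger effects above need 20–30% annual mortality across a whole covariate group together with fourfold stopping, and nothing in the protocol supports such mortality for, say, everyone aged 75–84.
- Removing the rule recovers only part of what is lost. In Illustration A's strongest case, total attenuation is ln 1.45 − ln 1.24 = 0.372 − 0.215 = 0.157. Of this, 0.372 − 0.247 = 0.125, about 80%, is present without the rule.
- The 2-year rule has a stated purpose: comparability with an earlier American study, and the longer gap that the outcome requires. It is secondary and is not offered as a clean contrast with the main analysis.

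These points limit the size and certainty of the bias. They do not supply a reason to exclude patients whom the planned methods can censor, and the 2-year analysis still changes population and outcome definition together.

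**Conclusion.** The point holds as one of design. Membership at entry is conditioned on later survival and registration, the planned methods do not need this, and no listed analysis would reveal its effect. Rates and HRs, the year-1 analysis in particular, would describe a narrower population than the protocol claims.

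The selection follows from the text; a material bias does not. Under the 1-year rule the effect on HRs runs from negligible to about half of a small log-HR (1.12 to 1.06), and every figure in that range rests on assumed loss and stopping rates. In Illustration A the 2-year rule costs more than the 1-year rule whenever frail patients stop more often, though that illustration uses the 90-day outcome, not the 365-day one. The change is worth making because it is cheap and removes the dependence on future events, not because a large bias has been shown.

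**What to change.** Replace observed with potential follow-up in Inclusion criteria: entry at least 1 year before the earlier of the study end and the practice's last upload date. Use 2 years in the same form for the 365-day-gap analysis. Dropping the criterion altogether would also do. Then:
- censor at death and deregistration, including in the first year;
- make censoring consistent with the window needed to see the outcome, for example by ending time at risk 90 days (or 365 days) before exit for everyone;
- state whether a first-year CVD diagnosis affects eligibility in primary prevention;
- keep the present restriction as a sensitivity analysis and report the numbers it removes, by reason.

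The cost is a change to one eligibility line, a matching change in Sensitivity analyses, and a somewhat larger cohort from the same extract. Some patients will contribute short follow-up, and stopping in the last 90 days before exit stays unascertainable under either rule. If the criterion is kept, the report should say that its results apply to patients alive and registered at 1 year (2 years for the long-gap analysis).
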